##### Oral health related quality of life

We will assess oral health-related quality of life using two measures. The Oral Health Impact Profile-14 is a 14-item scale designed to assess respondent’s perceptions of the impact of their oral conditions on their wellbeing.[19] Respondents indicate their agreement with a statement (Yes/No). Example items include: *“Do you feel your sense of taste has worsened because of problems with your teeth, mouth, or dentures?*” and” Have *you had to interrupt meals because of problems with your teeth, mouth, or dentures?”.* In a validation sample, the OHIP-14 has strong internal consistency (α = 0.88). Additionally, the 15-item European Organization for Research and Treatment of Cancer (EORTC)-Oral health module will be used. This questionnaire is designed to assess the conditions of informing oral health (e.g., bleeding gums, lip sores, taste change, sensitivity to food and drink). On items 1–11, respondents indicate agreement on a 4-point Likert Scale ranging from 1 (Not at all) to 4 (Very Much). On items 12–15, respondents indicate dichotomous agreement (Yes/No). Example items include, *“In the past week, have you had sores in the corner of your mouth?”* and *“Have you received any information about possible dental or mouth problems?”.* In an international validation study with cancer survivors, internal validity was acceptable (*α* = 0.79).

#### Secondary outcomes

Secondary outcomes of interest are related to systemic health and include systemic inflammation, overall quality of life, and comorbidities. Measures include collection of biospecimen, anthropometrics, and self-report measures. The target endpoint for secondary measures is 6-months, post-randomization.

#### Biospecimens

##### Saliva/DNA sample collection

Saliva samples will be collected to analyze the oral microbiome. Participants will first be instructed not to consume food or drink 30 min prior to assessment visit. Participant will self-collect (at baseline, 6- and 12-post randomization) the saliva sample (i.e., expectorate) using the Omnigene® Saliva DNA and RNA device (OMR-610). Saliva samples will be stored for up to 21 days at room temperature, and then will be stored at −20 °C. Samples will be processed by the Georgetown University Medical Center-Lombardi Comprehensive Cancer Center Tissue Culture and Biobanking Shared Resource (TCSBR) per manufacturers protocol using RNeasy Power Microbiome Isolation Kit to isolate human and bacterial DNA, and MagMax Viral/Pathogen Nucleic Acids Isolation kit to extract viral nucleic acid.

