## Interventions

### Explanation for the choice of comparators {6b}

Oral telehealth has shown clinically significant reductions in plaque, gingival inflammation, and the incidence of mouth sores (i.e., white lesions from oral mucositis), compared to conventional approaches [13]. Thus, its selection as a choice comparator is justified. While prior interventions have used asynchronous approaches, many have lacked personalization. This trial uses a synchronous approach to provide tailored feedback to aid individual participants in attaining the oral health goals.

Participants in the usual care arm will receive biweekly text messages which provide general health information and recommended practices about oral and systemic health.

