**Table Tabb:** 

Module Topic	Content
1. Connecting Oral and Systemic Health	Relationship between oral health and cancer outcomes Proper Brushing Technique Using Bass Method
2. Social Determinants of Oral Health	Common risk factors linking oral and systemic health Proper Flossing Technique
3. Diet and Oral and Systemic Health	Sugar and Oral Microbiome Healthy Hydration
4. Smoking and Alcohol and Oral and Systemic Health	Effects of Smoking on Oral and Systemic Health
5. Cancer Survivors, Oral and Systemic Health	Unique Oral Health Experiences of Cancer Survivors Managing Pain/Discomfort
6. Implementation for Long Term Maintenance	Completing Action Plan for Behavior Maintenance Celebrating Successes Exit Interview

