##### Intraoral Imaging

All participants, prior to randomization will undergo an intraoral imaging assessment. Intraoral imaging will be conducted on all study participants at the time of their baseline in-person visit using Mouthwatch® intraoral cameras. Photos of the mouth, teeth, and gums will be captured and saved in individual patient files for research and data purposes only. Images will be captured at 6- and 12-month follow-up assessment visits. We will have a dental consultant review the images and provide summary data. The World Health Organization oral mucositis toxicity scale will be used to assess oral images. The WHO Oral Toxicity Scale rates the anatomical, and function aspects of oral mucositis. The severity of oral ulcers and ability to consume food and liquid is reported on a scale of 0 (no presentation of symptoms) to 4 (not able to tolerate food or liquid diet). Higher scores indicate worse oral mucositis symptomology. To assess gingival inflammation, the Modified Gingival Index will be applied to intraoral images. We will rate inflammation of the gums on a 5-point Likert Scale ranging from 0 (absence of inflammation) to 4(severe inflammation, marked redness, edema. Higher scores indicate more severe inflammation.

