##### Blood Collection

Non-fasted blood samples will be collected to assess inflammatory markers including C-reactive protein, IL-1, IL-6, and TNF-alpha will be measured. Samples will be processed to separate plasma and buffy coat aliquots by GUMC-Lombardi TCBSR within two hours and stored at − 80 °C.

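### The saliva preparation rule covers only food and drink, so brushing, flossing or smoking just before a follow-up visit may differ by arm and could not be told apart from a lasting change in the oral microbiome

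*Protocol article*

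**What the plan says.** The protocol article, under Saliva/DNA sample collection, gives the purpose of the sample: "Saliva samples will be collected to analyze the oral microbiome". It then gives the preparation rule: "Participants will first be instructed not to consume food or drink 30 min prior to assessment visit". The section goes on to name the collection device, the storage limits and the extraction kits. No other restriction before the visit appears there or elsewhere in the article.

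The module table under Intervention description {11a} lists what the telehealth arm is taught. Module 1 includes "Proper Brushing Technique Using Bass Method", module 2 includes "Proper Flossing Technique", and module 4 covers "Effects of Smoking on Oral and Systemic Health". Goal-setting and tailored texts accompany the sessions.

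Implementation {16c} has the coordinator tell participants their allocation after baseline. On the comparator, section {6b} says: "Participants in the usual care arm will receive biweekly text messages which provide general health information and recommended practices about oral and systemic health".

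**The concern.** Saliva taken shortly after brushing, flossing or smoking may differ from saliva taken hours later. In most trials this would add similar noise to both arms. Here the behaviours that the rule leaves free are ones that the intervention sets out to change, and participants are not blinded. A telehealth participant who brushes and flosses just before the visit and a usual-care participant who last brushed the evening before both comply.

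What is at stake is the meaning of any microbiome comparison at 6 and 12 months. A difference could be a sustained change in the mouth, a trace of same-day cleaning, or both. Randomisation does not protect against this, because the behaviour arises after allocation and may depend on it. Adjustment for baseline does not help either, because baseline sampling precedes allocation.

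**Working it through.** **1. The passages side by side**

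| Question | Protocol article | Place |
|---|---|---|
| What is restricted before saliva sampling? | Food and drink, 30 minutes | Saliva/DNA sample collection |
| What is the telehealth arm taught? | Brushing, flossing, effects of smoking (mouthwash is not listed) | Module table, {11a} |
| Do participants know their arm? | Yes, told after baseline | {16c} |
| Does usual care get oral health advice? | Yes, general texts every two weeks | {6b} |
| When is baseline taken? | Before allocation | {16a} |
| Is recent cleaning recorded? | No item listed; smoking habits are surveyed, but no time since last cigarette is listed | Table 1; Health behaviors |
| Is the microbiome a named outcome? | No; biospecimens are listed as measures | Secondary outcomes |
| Is a microbiome model named? | No | {20a} |

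A difference between arms is therefore possible at 6 and 12 months but not at baseline. The documents establish the opportunity for it, not its occurrence.

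**2. The plan's own figure**

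Sample size {14} gives 45 per arm for d = 0.60 at 80% power and α = 0.05, and recruits 50 per arm to allow for 10% attrition. A two-sided two-sample t calculation also gives 45 per arm (power 0.804), and 45 / 0.90 = 50. The figure reproduces and is not in dispute. It is used below only to supply the number of evaluable participants.

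**3. Size of the artefact, under assumptions only**

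The documents give neither the share of participants who clean shortly before a visit nor the acute effect of doing so.

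Spurious difference in SD = (difference between arms in the share who cleaned recently) × (acute shift in SD).

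All inputs are assumed, with an acute shift of 0.5 SD:
- no difference in share: 0 × 0.5 = 0 SD
- 10 percentage points: 0.10 × 0.5 = 0.05 SD
- 30 percentage points (60% against 30%): 0.30 × 0.5 = 0.15 SD

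**4. What such a shift does to a comparison with no true effect**

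With 45 per arm, the standard error in SD units is √(2/45) = 0.211. For a shift b, the two-sided 5% error becomes Φ(b/0.211 − 1.96) + Φ(−b/0.211 − 1.96).

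| Assumed b (SD) | False-positive rate |
|---|---|
| 0 | 5.0% |
| 0.05 | 5.6% |
| 0.10 | 7.6% |
| 0.15 | 11.0% |
| 0.20 | 15.8% |

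This is a normal approximation for a single unadjusted comparison of means. It shows how sensitive such a comparison would be. It does not estimate the bias in this trial.

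**The case against.** **The article is condensed.** A fuller collection procedure, visit reminder or visit form may exist and may already cover oral hygiene. This stands as a limit: the article does not prove that no control exists. But it does not leave preparation to another document. It states a specific rule, in a section detailed enough to name the device and kits, and that rule is too narrow for an intervention of this kind.

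**The arm difference is presumed.** Usual care also receives oral health texts, and participants in either arm may clean before a visit where their mouth is photographed. Both could narrow the gap. Mouthwash is not in the listed module content, and less smoking in the telehealth arm would be partly an intended effect. All of this stands, and it is why the point is put as a possibility.

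**No named outcome is touched.** For saliva this is correct. The microbiome is collected at all three time points and is central to the Background, but it is neither a named outcome nor listed among the modelled measures.

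**A stronger reading.** A reader might infer that a primary outcome is also biased, because gum inflammation is rated from photographs and "Images will be captured at 6- and 12-month follow-up assessment visits". The documents do not support this. The Modified Gingival Index, as described, rates redness and swelling, not cleanliness. Nothing in the article shows that cleaning shortly before a photograph moves that score, or in which direction.

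A reader might also set the assumed 0.15 SD against the design effect of 0.60. That comparison means little, because the design effect rests on a quality-of-life result.

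**Conclusion.** The point holds for saliva, as a cheap improvement of low severity. As written, the rule lets brushing, flossing and smoking shortly before sampling differ by arm at 6 and 12 months, and the article lists no item that would allow this to be examined later. A microbiome difference could then not be attributed to a lasting effect of the intervention.

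The size is unknown and may be zero; the illustrative 0 to 0.15 SD rests wholly on assumed inputs. The conclusion assumes that the article states the rule in use and that recent cleaning or smoking affects the salivary sample, which the documents do not quantify. It does not affect the sample size or α, and the documents show no effect on a primary result.

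**What to change.** Extend the existing pre-visit instruction to tooth brushing, flossing, mouthwash and smoking as well as food and drink. Use one stated interval, the same in both arms and at all remaining visits. The article gives no basis for choosing its length, so the study team and the laboratory should set it. If a fuller collection procedure already covers this, a cross-reference is enough.

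At each visit, record the time since last oral cleaning and since last cigarette.

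Keep every randomised participant in the main comparison. Use the recorded times only to describe the arms or in a sensitivity analysis. Do not drop samples that break the rule: breaking it is behaviour after randomisation that may itself depend on arm, so exclusion could introduce selection bias and would depart from the planned intention-to-treat analysis.

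The cost is one sentence in the visit reminder, a couple of items on the visit form and slight inconvenience to participants. Visits already completed will have followed the old rule. The change should therefore start on the same date in both arms, and that date should be recorded. Trial status gives June 2026 as the end of recruitment, so 12-month visits for the last participants would fall around June 2027.

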##### Blood Collection

Non-fasted blood samples will be collected to assess inflammatory markers including C-reactive protein, IL-1, IL-6, and TNF-alpha will be measured. Samples will be processed to separate plasma and buffy coat aliquots by GUMC-Lombardi TCBSR within two hours and stored at − 80 °C.

#### Anthropometrics

Height: Participant height will be captured by a trained assessor, using a calibrated stadiometer. Height will be measured in centimeters and rounded to nearest tenth. Weight: Participant weight will be captured by a trained assessor, using a calibrated scale. Weight will be measured in kilograms and rounded to nearest tenth. Waist Circumference: Using tape measure, a trained assessor will measure the smallest portion of the participant’s waist in centimeters, rounding to the nearest tenth. Hip Circumference: Similar to waist circumference, hip circumference will be captured by a trained assessor measuring the widest part of the participant’s waist, rounding to the nearest tenth.

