##### Health behaviors

Dietary intake (including sugar-sweetened beverages [SSBs]), alcohol use, and smoking behaviors will be assessed using items from the widely-utilized Behavioral Risk Factor Surveillance Survey [21]. On dietary intake items, respondents will indicate their consumption of vegetables, fruits and fiber/whole grains. Item ratings include less than once/week; once per week, 2–3 times per week, 4–6 times per week, once/day, and more than once per day. Respondents will also indicate their daily meal patterns (i.e., average number consumed, and meal skipping). An example item includes: “*How often did you eat a green leafy or lettuce salad, with or without other vegetables?”.* Sugar-sweetened beverage consumption will be captured via 3 items, which assess consumption of SSB in past 7 days, average daily consumption, and knowledge of health implications of frequent consumption of SSBs. On alcohol use items, respondents will indicate number of alcoholic drinks consumed across lifespan, and within past 30 days. Item ratings include: 0 days, 1 or 2 days, 3–5 days, 3–9 days, 10–19 days, 20–29 days, and all 30 days. Lastly, smoking behaviors will be assessed via 4 items, which assess smoking behaviors across lifespan, daily smoking behaviors, and daily number of cigarettes consumed. Item ratings are similar to those of alcohol use.

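### As printed, hip circumference is sited at the waist and two past-30-day alcohol categories overlap at 3 to 5 days; both rules need correcting or checking, with minor impact

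*Protocol article*

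**What the plan says.** Under Anthropometrics, the protocol article gives a site for each girth. For waist, "a trained assessor will measure the smallest portion of the participant’s waist in centimeters, rounding to the nearest tenth". For hip, "hip circumference will be captured by a trained assessor measuring the widest part of the participant’s waist". Table 1 schedules both at 0, 6 and 12 months.

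Under Health behaviors, diet, alcohol and smoking "will be assessed using items from the widely-utilized Behavioral Risk Factor Surveillance Survey". For alcohol, "respondents will indicate number of alcoholic drinks consumed across lifespan, and within past 30 days", and the answer options are "0 days, 1 or 2 days, 3–5 days, 3–9 days, 10–19 days, 20–29 days, and all 30 days". For the smoking items the article adds: "Item ratings are similar to those of alcohol use". Table 1 schedules alcohol and smoking at the same three visits, and its footnote gives change from baseline as the analysis metric.

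Under Secondary outcomes, the article states: "Measures include collection of biospecimen, anthropometrics, and self-report measures". The outcomes it names there are inflammation, overall quality of life and comorbidities.

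**The concern.** Both passages are operative rules for how data are recorded, and both are wrong as written.

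The hip rule names the waist. If it is followed, the field labelled hip circumference holds a second waist girth. A hip value that was never taken cannot be recovered from two waist values, so such entries could not be reported as hip circumference or used in any index that needs it.

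The alcohol options offer two boxes to a person who drank on 3, 4 or 5 days. An answer of 3–9 then does not tell the analyst whether the true count is 3 to 5 or 6 to 9, and a change within that range can be missed. If the smoking options were built on the same list, they could carry the same overlap.

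**Working it through.** The article states no figure to reproduce here. The check is a reading of the two girth rules and a count of the categories.

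**Hip rule (Anthropometrics section)**

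| Measure | Body region named | Point on that region |
|---|---|---|
| Waist circumference | Waist | Smallest |
| Hip circumference | Waist | Widest |

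The region is the same in both rows and only the point differs. No other sentence in the article gives a hip site. Read literally, the protocol yields two waist girths and no hip girth. With 100 participants (Sample size section) and three visits (Table 1), the most entries that could be exposed is 100 × 3 = 300. That is a ceiling: it assumes every assessor follows the literal text and nobody misses a visit.

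**Alcohol categories (Health behaviors section)**

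The possible answers are the whole numbers 0 to 30, that is 31 counts. If the categories neither overlap nor leave gaps, their widths must add up to 31.

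| Version | Widths in order | Sum |
|---|---|---|
| As printed: 0; 1–2; 3–5; 3–9; 10–19; 20–29; 30 | 1 + 2 + 3 + 7 + 10 + 10 + 1 | 34 |
| Second of the pair read as 6–9 | 1 + 2 + 3 + 4 + 10 + 10 + 1 | 31 |
| 3–5 and 3–9 merged into 3–9 | 1 + 2 + 7 + 10 + 10 + 1 | 31 |

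The excess as printed is 34 − 31 = 3. Going through each count from 0 to 30 shows which they are: 3, 4 and 5 each fit both 3–5 and 3–9. The remaining 31 − 3 = 28 counts fit exactly one category, and no count is left out. Under either repair every count fits exactly one category.

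**What this does to a change score**

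A participant who goes from 8 days to 4 days has only 3–9 available at the first visit and either 3–5 or 3–9 at the second. If 3–9 is chosen again, no change is recorded. If 3–5 is chosen, the change is visible. After merging to 3–9 the answer no longer depends on which box was picked, but movement within 3 to 9 days cannot be seen at all.

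**A further mismatch in the same paragraph**

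The description of the alcohol items asks for a number of drinks, over the lifespan and over 30 days, while the options count days. This should be settled in the same check of the form.

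**The case against.** The strongest reply is that these are drafting slips in a condensed article. The hip measure has its own label, is listed separately from waist and is assigned to a trained assessor; the section on assessment and collection of outcomes describes trial-specific training with mock assessments. The wording looks carried over from the waist sentence just before it. The alcohol items are taken from an existing survey, so 3–9 may be a one-digit misprint for 6–9 that never reached the Qualtrics form. Neither the assessor manual nor the live survey is shown. All of this stands: the article does not establish that a single value was recorded wrongly.

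A reader might infer that neither variable can be used as recorded. The documents do not support that. For alcohol, merging two categories restores a clean ordinal scale without new data, at some loss of detail. For hip, the conclusion would need evidence that assessors measured at the waist, and there is none.

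A reader might also infer damage to a planned result. The repeated-measures models in the statistical methods section name neither measure, and no waist-to-hip analysis appears anywhere. The ANCOVA is described generically for each outcome measure, which does not single out hip or alcohol. Module 4 has alcohol in its title, but its listed content concerns smoking only, so a masked intervention effect on drinking would be a thin claim. The smoking ratings are called similar, not identical, so carry-over is a possibility to check and no more.

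What the reply does not remove is the text itself. The hip site and the category list are wrong as printed, whatever was done in practice.

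**Conclusion.** The point holds as a minor correction. As printed, the hip rule produces no hip girth, and the alcohol options place 3 of 31 day counts in two categories. The effect is confined to the hip and alcohol measures, and possibly smoking. None of these is a primary outcome, a named secondary outcome or an input to the sample size.

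Two matters remain open. Whether data were collected under the printed rules depends on the assessor manual and the administered form. That 6–9 was the intended category is an inference from the gap-free sequence; the article does not say so. The conclusion that the text needs correcting depends on neither.

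**What to change.** 1. In the Anthropometrics section, site hip circumference at the widest part of the hips or buttocks. Check the assessor manual and training materials for the same wording.
2. Ask assessors where they have been measuring. Flag any value taken at the waist as not hip, and keep it out of any hip summary.
3. Compare the alcohol options, and the smoking options described as similar, with the administered Qualtrics form and the source items. Settle at the same time whether the alcohol item counts drinks or days.
4. If the overlap exists only in the article, correct the article. If it is live, make the categories distinct in the form (probably 6–9 days, once confirmed), and merge 3–5 and 3–9 into one 3–9 category for data already collected. A participant with visits on both versions of the form should be compared on the merged scale.

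The cost is two wording corrections, a check of the manual and the survey build, and a short reminder to assessors. The only statistical cost is the lost detail within 3 to 9 days, and it arises only if the overlap was live. Recruitment is stated to run from May 2024 to June 2026 with follow-up to 12 months, so a correction made while visits continue protects the later measurements.
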